## Abstract

**Background:**

Transitioning from the burn unit to the home/community can be chaotic with limited professional support. Some adult burn survivors may face varied concerns leading to poor outcomes in the early post-discharge period with limited access to professional help. Based on these, a nurse-led transitional burns rehabilitation programme has been developed and the current trial aims to ascertain its effects as well as explore the implementation process.

**Methods:**

A single-centre, double-arm randomised controlled trial with a process evaluation phase will be utilised for this study. All adult burn survivors aged ≥ 18 years with burn size ≥ 10% total burn surface area at the site during the study period will be screened for eligibility at least 72 h to discharge. A sample size of 150 will be block randomised to treatment (receiving the nurse-led transitional care programme and routine post-discharge service) and control groups (receiving routine post-discharge service). The nurse-led transitional care programme comprises of predischarge and follow-up phases with the delivery of bundle of holistic interventions lasting for 8 weeks. There are three timelines for data collection: baseline, immediate post intervention, and 4 weeks post-intervention.

**Discussion:**

The findings from this study can potentially inform the development and organisation of post-discharge care and affirm the need for ongoing comprehensive home-based care for burn survivors and their families

**Trial registration:**

ClinicalTrials.govNCT04517721. Registered on 20 August 2020

## Background and rationale

Burns are one of the most devastating forms of injuries that primarily affect the skin [1]. Depending on the extent of the injury, a burned patient may require critical care to resolve physiological alterations. As care progresses during emergent/acute phase, rehabilitation that occurs concurrently can promote recovery [2–4]. Rehabilitation minimizes the adverse consequences of the burn by improving functional ability, enhancing psychological well-being, facilitating early return to work/school and improving quality of life [5]. As rehabilitation occurs, the burn patient is able to attain a degree of pre-injury abilities as closely as possible [6, 7] and is able to do things that are desirable to them as recover progresses [8, 9].

Along the recovery trajectory for burn survivors, previous studies have observed that the greatest physical and psychosocial decline may be experienced following discharge [10–12]. Concerns regarding pain, anxiety, and uncertainties about return to work/community integration may emerge immediately following discharge [13, 14]. By 2–3 months post-discharge, burn survivors may experience increasing depression/anxiety levels, itchiness associated with healed wounds, pain, poor sleep, scarring, and difficulties with physical functioning/performance leading to poor quality of life in the absence of rehabilitative support commensurate to their needs [13, 15, 16]. By 6–12 months post-discharge, the burn survivor may experience further distress reflected by the high rates of depression, sleep disturbances, body image concerns, and posttraumatic stress disorder [16–18]. Taken together, these may suggest that the transitional period from the immediate pre-discharge to the early post-discharge phase represent a vulnerable stage which can impact long-term recovery outcome [14].

Despite the emergence of varied needs following discharge, there is often limited communication, lack of coordinated and continuous professional support as the burn patient transits from hospital to the home/community [13, 14, 19]. Home care and support may become chaotic, often with limited access to professional support. Some burn survivors may not also return to the hospital for follow-up care due to long travel distances and associated costs. Comprehensive follow-up system of care in the home/community is therefore greatly needed to promote rehabilitation of burn survivors [20]. It is worth mentioning that the home/community has been identified as a suitable location for the implementation of burn rehabilitation programmes which can enhance patient outcomes, particularly if the programme is structured and have active follow-ups on the burn survivor [21].

In Mainland China, the concept of burns rehabilitation is new to some provinces [22], and only in recent years that rehabilitation of the burn patient was considered an integral part in the Chinese burn care system [23]. Where available, it has been observed that significant challenges exist which include lack of hospital support with no standardised rehabilitation guidelines, inadequate rehabilitation knowledge among practitioners, human resource shortages, limited funding, and financial burden on the burn patients [24]. The rehabilitation protocols, if available, usually focus primarily on the physical aspects of the injury which leaves limited room to attend to the psychosocial concerns of the patient recovering from burns [25]. Consequently, burn patients may not have adequate rehabilitative care as inpatients and with limited support following discharge which adversely affects their recovery process. Thus, to bridge the immediate pre-discharge and early post-discharge gap aiming to improve patient outcomes, a nurse-led transitional burns rehabilitation programme (4Cs-TBuRP) has been developed following the Medical Research Council (MRC) Framework [26] (see Fig. 1, a tentative logic model underpinning the intervention).

**Fig. 1 Fig1:**
[figure not shown]
Tentative logic model

Developing the intervention proceeded through extensive literature reviews [27–29], exploratory studies, and expert consultations. The current phase seeks to evaluate the effectiveness of the programme in comparison to the existing standard of care. The 4Cs in the intervention represent comprehensiveness, coordination, collaboration, and continuity, which were proven to be essential transitional care elements tested among patients with chronic conditions [30–32]. The 4Cs emphasise on the need for ongoing holistic care required by burn survivors throughout the recovery trajectory. We ask if the nurse-led transitional rehabilitation programme underpinned by multi-disciplinary support can improve quality of life of burn patients, the primary outcome, in the first 12 weeks following discharge. As secondary outcomes, we will investigate the effects on psychological functioning, sleep patterns, itchiness, pain, and physical role functioning. This study protocol was completed in accordance with the SPIRIT 2013 guidelines [33].

## Objectives

The trial will explore the effects and implementation process of a nurse-led transitional rehabilitation programme for adult burn survivors. We seek to evaluate the effects of a nurse-led transitional rehabilitation programme on the following outcomes among adult burn survivors:
Quality-of-life (primary outcome)Psychological functioningSleep patternsItchinessPainPhysical role functioning/performance

A secondary objective of this study is to examine the process involved and issues encountered during the implementation of the transitional rehabilitation programme.

## Trial design

The trial is a double-arm (intervention and control groups), single-centre randomised controlled trial with 1:1 allocation ratio and a follow-up process evaluation phase. We will firstly undertake a pilot feasibility phase and follow-up with the full-scale trial. The null hypothesis is that there will be no difference regarding outcomes between the intervention and control groups. The alternative hypothesis is that there will be statistically significant differences between the participants undergoing the nurse-led programme of care and participants receiving the existing standard of care.

The follow-up process evaluation phase will employ a multi-method approach (qualitative and quantitative strands) to examine the process and issues during the implementation process [34]. Twelve process measures covering domains such as recruitment, follow-up, intervention delivery, and data collection will be considered in the process evaluation phase (see Table 1). The qualitative strand will capture changes in the implementation process and experiences with the intervention from the perspectives of adult burn survivors and nurse case managers. The quantitative strand will offer insight into key process variables such as recruitment, follow-up, and adherence rates. Details regarding the process evaluation phase (process measures, variables, methods, and participants) are provided in Table 1.

**Table 1 Tab1:** Outline of process evaluation for the nurse-led transitional rehabilitation program

Process measures	Process variables	Method	Participants and data collection method
Recruitment and selection rate	• Number of burn survivors screened at the study setting. • Number of participants from the sample of eligible persons. • Number of participants versus aimed number	Enrolment record review	Site manager (research team member)/data collection team
Barriers and facilitators in recruitment and selection process	• Motivation of participating eligible persons. • Experience with recruitment and selection	Semi-structured interviews	Adult burn survivors Recruiting nurses
Follow-up and attrition rate	• Number of participants completing follow-up	Follow-up record review	Site manager (research team member)/data collection team
Barriers and facilitators for follow-up	• Reasons for drop-out • Motivation for continued participation	Semi-structured interviews	Adult burn survivors
Quality of delivery of the interventional components	• The part of each component and the complete intervention delivered by nurse case managers • Satisfaction with delivery	Semi-structured interviews	Nurse case managers
Barriers and facilitators for delivery of interventional components	• Reasons for deviating from, or applying components as planned	Semi-structured interviews	Nurse case managers
Adherence to interventional components	• Number of sessions followed • Intervention components fully implemented and rationale • Intervention components partly implemented and rationale • Intervention components not implemented and rationale • Compliance to individual recommendations	Semi-structured interviews	Adult burn survivors and nurse case managers
Barriers and facilitators for adherence to interventional components	• Motivation for (or lack of) compliance	Semi-structured interviews	Adult burn survivors and nurse case managers
Experience of participants and nurse case managers with the components of the nurse-led interventions and training programme for the nurses.	• Perceived benefit v actual benefit • Strong and weak aspects of the interventional components (structure and content) • Experiences with the educational component (adequacy in assisting burn care nurses to deliver the intervention)	Semi-structured interviews	Adult burn survivors (in intervention group) and nurse case managers
Experience of participants with clinical outcomes associated with the intervention.		Semi-structured interviews	Adult burn survivors (in intervention group)
Completeness of data collection	• Reasons why data were missing • Reasons why participants were excluded from analysis	Semi-structured interviews	Data collection team
Barriers and facilitators for data collection		Semi-structured interviews	Data collection team

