### Strategies to improve adherence/fidelity of the intervention

Fidelity will be ensured in this study by using the guidelines offered by Bellg et al. [36] which comprises of (1) ensuring that the intervention dose is the same for all participants across each condition, (2) standardising interventionist training, (3) monitoring the intervention delivery, (4) evaluating participants’ understanding of information provided, and (5) ensuring that participants use the skills taught in the intervention. Adherence reminders will also be given every week to participants during the follow-up via WeChat or telephone. Burn care nurses will document date and length of contacts per participant, referrals to specialists, and performance of intervention components. All calls will be documented, and WeChat messages/images will be reviewed by the team on monthly basis. Also, the care plan sheets for each participant will be reviewed by the research and clinical team via case conferencing held bi-monthly to discuss assessment, management, and evaluation in relation to the study protocol. Nurse case managers will be encouraged to maintain a clinical diary which will be reviewed.

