### Sampling and sample size estimation

Subjects will include adult burn survivors with burn size ≥ 10% TBSA from the Burn Unit. Upon recruitment, randomisation to either control or treatment group (ratio 1:1) with a blinded approach will be carried out. For the pilot phase of the project, the pilot feasibility sample size rule suggested by Whitehead, Julius, Cooper, & Campbell will be used [50]. The rule specifies that a total sample size of 25 participants per arm. Considering possible attrition rate of 20% that has been reported in burn care literature implies that an additional 5 participants will be added to both arms summing up to 30 participants per arm (total = 60 participants).

For the main trial, the sample size calculation based on the primary outcome measure (Burn Specific Health Scale) at 95% confidence level, 90% statistical power and moderate effect size will yield a total of 38 participants per arm [51–53]. Considering an attrition rate of 20%, the final sample size will be 45 participants per arm (total = 90 participants). In all, 150 participants will be recruited for the entire study. For the follow-up process evaluation phase, we will conveniently recruit up to fifteen [15] participants from each arm whilst being guided by the principle of data saturation in addition to the burn care nurses delivering the intervention to complete the qualitative strand. Data saturation will be determined at the point where no new data emerges. The quantitative strand will include review of the recruitment, enrolment, and follow-up records.

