## Data collection, management, and analysis

### Data collection methods and management

All outcomes will be assessed at baseline (T0); that is after the patient has been recruited. Following the completion of the intervention, the second phase of data collection (T1) will be undertaken; that is at the 8th week. The third phase of data collection (T2) will be the follow-up phase at 4 weeks post-intervention. Data collection will be in the form of completion of questionnaires. The data collection process will be undertaken by three research assistants who will be blinded to the groups of the participants. The research assistants have completed a 10-h training programme covering the outcome measures to be used. Following the training, they undertook a role play to enable the research team to ascertain the inter-rater reliability/percentage agreement with the following results: Burn Specific Health Scale-B (87.7%), EQ-5D-5L (100%), HADS (92.5%), PSQI (86.7%), DASH (84.4%), VAS (100%), BPI (100%), and VSS (100%). All quantitative data will be entered and stored in SPSS Version 25 (SPSS, an IBM company, Chicago, Illinois, USA). All hard copies of documents relating to the study will be stored under lock and key only accessible to designated research team member.

For the follow-up process evaluation phase (qualitative strand), face to face semi-structured interviews with an interview guide will be utilised to collect data after the intervention period has elapsed. Topics for the interview guide will be based on the process evaluation components as highlighted in Table 1. All interview proceedings will be audiotaped and transcribed verbatim in the Trint Automated Transcription Software. Interview transcripts will be exported to QSR NVivo version 10 will be used to manage the data. All soft files related to the study will be kept in a password protected computer only accessible to the principal investigator and the doctoral student investigator. Paper files will be kept under lock and key. For the quantitative phase, we will review the recruitment, enrolment, and follow-up records.

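### Adherence rates are promised from the quantitative strand, but Table 1 assigns the countable adherence and delivery items to interviews and not to the per-participant records already kept

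*Protocol article*

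**What the plan says.** All references are to the Protocol article.

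- Objectives: "A secondary objective of this study is to examine the process involved and issues encountered during the implementation of the transitional rehabilitation programme".
- Trial design, on what the quantitative strand will yield: "The quantitative strand will offer insight into key process variables such as recruitment, follow-up, and adherence rates". The text then refers the reader to Table 1 for measures, variables, methods and participants.
- Table 1, adherence row: the variables begin with "Number of sessions followed • Intervention components fully implemented and rationale" and go on to components partly implemented and not implemented. The method is semi-structured interviews; the sources are adult burn survivors and nurse case managers.
- Table 1, quality-of-delivery row: the first variable is "The part of each component and the complete intervention delivered by nurse case managers". The method is again semi-structured interviews, and the only source is the nurse case managers.
- Table 1 uses record review in two rows only: recruitment, and the number completing follow-up.
- Sampling and sample size estimation, on the interviewees: "we will conveniently recruit up to fifteen [15] participants from each arm whilst being guided by the principle of data saturation". The nurses delivering the intervention are interviewed as well.
- Data collection methods and management: "For the quantitative phase, we will review the recruitment, enrolment, and follow-up records". Sampling and sample size estimation describes the quantitative strand in the same terms.
- Strategies to improve adherence/fidelity of the intervention: "Burn care nurses will document date and length of contacts per participant, referrals to specialists, and performance of intervention components". The same section has calls documented, WeChat material reviewed monthly and each participant's care-plan sheets reviewed at case conferences.

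**The concern.** A count of sessions and the implementation status of each component are quantities. They need a complete, consistently recorded source with a known denominator. Table 1 gives them a qualitative method, while the text promises a rate from a strand whose listed records do not clearly contain the information. Of the three rates that Trial design names, recruitment and follow-up have a record source in Table 1 and adherence has none.

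The implementation process is a stated secondary objective, and how much of the programme was received is a central part of it. If the team follows Table 1 as written, the adherence result will be what a self-selected minority of programme participants and their own nurses remember. The fuller record made during delivery would have no planned use in the process evaluation.

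**Working it through.** The 15 per arm is a saturation-guided ceiling with no formula behind it, so there is no stated figure to reproduce. The check sets the sources side by side and then looks at coverage.

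**1. Source named for each rate promised in Trial design**

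- Recruitment: Table 1, enrolment record review. Consistent with the promise.
- Follow-up: Table 1, follow-up record review, tied to the number completing follow-up. Consistent.
- Adherence: Table 1, interviews only. No row gives a record source, and neither description of the quantitative strand names contact logs, care-plan sheets or call records. Not consistent.

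**2. Who can report adherence in interviews**

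- Total sample: 60 (pilot) + 90 (main) = 150. At 1:1 this is 30 + 45 = 75 per arm.
- Control participants do not receive the programme, so only the programme-arm interviewees can report adherence to it: at most 15.
- Coverage: 15/75 = 20% over pilot and main trial, or 15/45 = 33% if only the main trial counts. The article does not say which applies. Both are ceilings, because saturation may stop recruitment earlier.
- Second source: the delivering nurses. Eligibility criteria says two burn care nurses primarily provide the programme. Their accounts can in principle span the whole arm, but only as recall of their own work.

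**3. Who is covered by the delivery records**

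The nurses document contacts and component performance per participant, and under Blinding they deliver only to the treatment group. The records should therefore cover all 45 or 75 programme participants, against at most 15.

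**4. What the difference in denominator means (illustration only)**

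The article gives no adherence rate, so a range of 50% to 90% is assumed. Wilson 95% interval, z = 1.96:

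centre = (p + z²/2n)/(1 + z²/n)

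half-width = z·√(p(1−p)/n + z²/4n²)/(1 + z²/n)

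- n = 15: half-width 22.6 points at 50%, 15.8 at 90%; at 80% the interval is 54.8% to 93.0%.
- n = 45: half-width 14.0 at 50%, 9.0 at 90%; at 80%, 66.2% to 89.1%.
- n = 75: half-width 11.0 at 50%, 6.9 at 90%; at 80%, 69.6% to 87.5%.

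Worked for p = 0.8, n = 15: centre = (0.8 + 0.128)/1.256 = 0.739; half-width = 1.96 × √(0.01067 + 0.00427)/1.256 = 0.191.

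The protocol does not plan to estimate a proportion from the 15, and a convenience sample does not meet the random-sampling assumption of these intervals. They show only why such a sample should not be made to serve as the source of a rate.

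**The case against.** The best defence is that this is loose wording in a table headed as an outline. The text assigns adherence rates to the quantitative strand, and the per-participant records exist. Because the programme's post-discharge part is itself called the follow-up phase, follow-up records could be read to include the contact logs. That reading is possible, but Table 1 links follow-up record review to the number completing follow-up and gives adherence a different method. The two statements still have to be reconciled.

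A reader might also infer four stronger things that the article does not support:

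- **That delivery is measured in the 15-per-arm sample.** It is not. Its source is the nurse case managers, who are also a second source for adherence.
- **That a null trial result could not be interpreted.** The records are kept for every programme participant and could be analysed. What is missing is a stated plan to do so.
- **That the per-protocol set depends on interviews.** Statistical methods and analysis defines it by completion of the entire intervention and does not say that completion is established by interview.
- **That interviewees will all be completers, so adherence will look perfect.** Table 1 plans to ask about reasons for drop-out and lack of compliance, so non-completers are meant to be reached. For illustration with invented figures: if 60 of 75 completed, true completion would be 80%, and a completers-only sample would show 100%. That is a worst case, not an expectation. Selection towards adherent volunteers is a plausible risk and no more.

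It is also fair to say that the logs are written by the same nurses, so moving to them does not remove self-report.

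**Conclusion.** The point stands as a mismatch between stated method and variable. Adherence rates are promised from the quantitative strand, while Table 1 assigns the countable adherence and delivery items to interviews alone. The burn-survivor interviews reach at most 20% of the programme arm (33% if only the main trial counts), chosen by convenience, and the nurse interviews rest on recall by the providers. Neither can give an arm-wide adherence rate.

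This rests on reading follow-up records as Table 1 uses the term, and on the fidelity documentation being kept for every programme participant, as its wording indicates. It affects the secondary objective only. The efficacy outcomes, randomisation and sample size are untouched. It should be corrected because the better source is already being created.

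**What to change.** - In Table 1, change the method for sessions followed, for components fully, partly or not implemented, and for the part of each component delivered to review of contact logs, care-plan sheets and call records for all programme participants.
- Keep interviews for rationale, barriers and facilitators, satisfaction and experience, where they suit the question.
- Name these records as part of the quantitative strand in Sampling and sample size estimation and in Data collection methods and management.
- State that the same records supply completion status for the per-protocol set.

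Cost: a wording change and a modest amount of tabulation, with no new data, visits or staff. One limitation remains, since the logs are still nurse-written. They are, however, made as the programme is delivered, and Table 3 has several contacts recorded, so a sample of entries can be checked against the recordings.
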